## Abstract

**Background:**

Young Australians aged between 18 and 30 years have experienced the largest increase in the body mass index and spend the largest proportion of their food budget on fast food and eating out. Frequent consumption of foods purchased and eaten away from home has been linked to poorer diet quality and weight gain. There has been no Australian research regarding quantities, type, or the frequency of consumption of food prepared outside the home by young adults and its impact on their energy and nutrient intakes.

**Objectives:**

The objective of this study was to determine the relative contributions of different food outlets (eg, fast food chain, independent takeaway food store, coffee shop, etc) to the overall food and beverage intake of young adults; to assess the extent to which food and beverages consumed away from home contribute to young adults’ total energy and deleterious nutrient intakes; and to study social and physical environmental interactions with consumption patterns of young adults.

**Methods:**

A cross-sectional study of 1008 young adults will be conducted. Individuals are eligible to participate if they: (1) are aged between 18 and 30 years; (2) reside in New South Wales, Australia; (3) own or have access to a smartphone; (4) are English-literate; and (5) consume at least one meal, snack, or drink purchased outside the home per week. An even spread of gender, age groups (18 to 24 years and 25 to 30 years), metropolitan or regional geographical areas, and high and low socioeconomic status areas will be included. Participants will record all food and drink consumed over 3 consecutive days, together with location purchased and consumed in our customized smartphone app named Eat and Track (EaT). Participants will then complete an extensive demographics questionnaire. Mean intakes of energy, nutrients, and food groups will be calculated along with the relative contribution of foods purchased and eaten away from home. A subsample of 19.84% (200/1008) of the participants will complete three 24-hour recall interviews to compare with the data collected using EaT. Data mining techniques such as clustering, decision trees, neural networks, and support vector machines will be used to build predictive models and identify important patterns.

**Results:**

Recruitment is underway, and results will be available in 2018.

**Conclusions:**

The contribution of foods prepared away from home, in terms of energy, nutrients, deleterious nutrients, and food groups to young people’s diets will be determined, as will the impact on meeting national recommendations. Foods and consumption behaviors that should be targeted in future health promotion efforts for young adults will be identified.

## Introduction

### Background

Overweight and obesity rates continue to rise globally [1]. In Australia, more than 63% of adults are overweight or obese [2]. Increased body weight is associated with the incidence of a number of chronic diseases, and the estimated direct costs of overweight and obesity in Australia is AUD $21 billion per year [3].

Studies have demonstrated that the rate of weight gain in today’s young adults has been faster than any other birth cohort [4]. In Australia, males aged 20 to 24 years have the highest annual rate of increase in body mass index (BMI) among all age groups across the life span, and for women, 20 to 29 years is the period of greatest weight gain [5]. Those living in rural areas and of lower socioeconomic status (SES) and lower educational attainment are at higher risk of obesity [6]. The transition from high school to university places students at risk of marked weight gain [7]. The international literature shows that students are likely to gain 1.36 kg in their first 5 months of tertiary education, with more than 60% gaining an average 3.38 kg in the first year [7].

In Australia, young adults are the most frequent consumers of fast foods [8] and spend the largest proportion of their household food budget on fast foods and eating out [9]. In the United Kingdom and the United States, young adults (younger than 35 years) have the highest intakes of foods prepared outside the home [10].

Food environments that promote consumption of highly processed, energy-dense, and nutrient-poor foods and drinks are a major contributor to overweight and obesity levels across all age groups [11]. Frequent consumption of foods prepared outside the home, be it at fast food joints or restaurants, results in poorer diet quality and is associated with weight gain [12-15], insulin resistance [16], diabetes [17], and depression [18-20].

### Knowledge Gaps

Although foods purchased and eaten away from home can impact nutritional status [13,21], the most recent Australian National Nutrition and Physical Activity Survey did not collect data on the source of the food and beverages consumed [22]. Limited research has focused on specific food types that may or may not have been sourced outside the home [23] or on determinants of fast food intake [8,24]. Only one Australian study has been conducted on the consumption of foods purchased outside of home and how this affects the total diet [25]. However, that analysis was conducted using data collected more than 20 years ago, and as Australians’ expenditure on fast foods and eating out has been increasing [9], as have the rates of overweight and obesity, it is timely to revisit the role of eating out on diet quality and risk factors for chronic disease. The exact quantities, type, and frequency of consumption of food prepared outside home by young adults and the impact this has on their energy, macronutrient, and micronutrient intakes is currently unknown. To address these gaps in knowledge, the proposed project will collect data on the frequency, type, amount, and place of purchase of foods prepared away from home, together with sociodemographic data in a population sample of 18- to 30-year-old Australians.

## Methods

### Aims

The study will determine how frequently young adults purchase and consume foods away from home in the context of their entire diet, and what types of foods they are purchasing and consuming. The relative contributions of different food outlets (eg, fast food chain, independent takeaway food store, coffee shop, restaurant, cafeteria) to overall food and beverage intake of young adults will be established. Finally, the extent to which food and beverages consumed away from home contribute to the total energy and nutrient intake of young adults will be determined using the complete 3-day food and beverage intake data records.

As a substudy, the comparative validity of data collected by the app will be determined using the 24-hour recalls.

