Once participants have recorded the foods and drinks they consumed, they then enter the amounts ingested into the EaT app (Figure 3), together with the location from which the food was sourced (Textbox 2). Participants were instructed to choose “home” for all foods not purchased and consumed outside the home. While not mandatory, participants are encouraged to weigh and measure the foods and drinks before consumption, and there is a check button to indicate if foods have been weighed. If not weighed, participants are encouraged to use the Food Model booklet to estimate their amounts in household measures, or they can enter a default portion size. These default sizes are based on typically consumed portion sizes for males and females aged 18 to 30 years based on the latest national dietary survey [41]. If participants cannot find a food listed in the app’s database, they will be able to manually enter it as a new food, and this will be flagged to the research team for follow-up. Each entry is time and date stamped, and thereby indicates whether all entries are made at one time or recorded prospectively throughout the day.

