**Figure 3 figure3:**
[figure not shown]
Eat and Track (EaT) app screenshots showing the landing screen, food logging screen, and pink button filtering of foods.

Locations for food source included in the Eat and Track App.Fast food chain (Chain outlets selling takeaway foods, such as burgers, pizza, or fried chicken)McDonald’s, KFC, Pizza Hut, Mad MexCoffee chain (Chain outlets selling predominantly coffee and tea)Gloria Jean’s Coffee, StarbucksCold drink chain (Chain outlets selling predominantly cold drinks, including juice, smoothies, or iced tea)Boost Juice, EasyWay TeaIce creamery/frozen yogurt (Chain or independent outlets selling predominantly ice cream, gelato, or frozen yogurt)New Zealand Natural, Yogurberry, local ice creameryOther takeaway (Independent outlets selling any type of takeaway foods)Local fish and chip shop, local pizzeriaIndependent café or restaurant (Independent sit-down café or restaurant selling any type of cuisine; may also do takeaway food)Asian/Indian restaurant, local café, other restaurantsBakery or patisserie (Chain or independent outlets selling predominantly baked goods, such as cakes, breads, and sweets)Michel’s Patisserie, Muffin Break, local bakeryService station/convenience store (Food bought from service stations or convenience stores, including cafes in these locations)7-Eleven, Wild Bean Café, or BP, Shell or Mobil service stationsPub or club (Restaurants, bars, cafes or bistros in pubs or clubs)Bowling, RSL, sports or community clubs, local hotelsHome (Any food not sourced from the locations above.)Includes homemade food, food prepared by friends or relatives, or foods purchased from supermarkets

At the conclusion of each day’s recording, participants will complete a short survey. This survey will determine whether the day’s food and beverage intake, frequency of eating away from home, physical activity, stress, and sleep levels were higher or lower than usual. Additionally, self-reported healthiness of the day’s dietary intake, assessed by a 5-point Likert scale, ranging from “very unhealthy” to “very healthy” was included in the end of day survey.

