#### Consumption of Foods Purchased and Eaten Away From Home

The average frequency of meals, drinks, and snacks (collectively, and by occasion) purchased and eaten away from home will be calculated. Multivariate regression models will be used to determine the health, social, and environmental factors associated with consumption of foods purchased and eaten away from home. The relative contribution of foods purchased and eaten away from home to total energy and macronutrient intake will be calculated.

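### The aims name cafeterias, but the app's source list has no cafeteria or general away-from-home code, and its definition of Home conflicts with the instruction given to participants

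*Protocol article*

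**What the plan says.** The Aims section states that the study will establish how much is contributed by "different food outlets (eg, fast food chain, independent takeaway food store, coffee shop, restaurant, cafeteria", relative to everything young adults eat and drink.

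The section on the Eat and Track app says that, for each item, participants enter the amount and pick a source from the list in Textbox 2. The same section gives the rule for the Home option: "Participants were instructed to choose “home” for all foods not purchased and consumed outside the home".

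Textbox 2 then lists ten options:
- nine outlet types: fast food chain, coffee chain, cold drink chain, ice creamery or frozen yogurt, other takeaway, independent café or restaurant, bakery or patisserie, service station or convenience store, and pub or club;
- Home, defined as a residual that takes any food not obtained from those nine. Its description continues: "Includes homemade food, food prepared by friends or relatives, or foods purchased from supermarkets".

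The outcome that depends on this coding appears in the last part of the Statistical Analysis section: "The relative contribution of foods purchased and eaten away from home to total energy and macronutrient intake will be calculated". Frequency of eating out and the regression models in that part use the same coding.

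**The concern.** An outlet type that the aims name has no code in the instrument that records outlet type. The list also lacks a neutral place for outlets that nobody foresaw, such as vending machines. Its only residual is Home, which is the comparison category of the study. Food that is bought out but fits none of the nine descriptions is then scored, under the list's own definition, as the opposite of what it is.

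The participant instruction says something different, so two rules for the key classification are in force at once. At stake are the away-from-home frequency, the energy and macronutrient shares, and the outlet breakdown. This is more than detail that an article would leave to a fuller document, because the article prints the list with its definitions and the definitions disagree with the text around them.

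**Working it through.** The check is mainly textual, since the plan gives no figure to reproduce.

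**Step 1: is there a code for a cafeteria?** The two nearest categories in Textbox 2 are Other takeaway and Independent café or restaurant. Both are described as independent outlets, the first selling takeaway food and the second offering sit-down service. Neither mentions a workplace, campus or institutional canteen. Other takeaway is not a general away-from-home code, because it is limited to independent takeaway outlets.

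**Step 2: where does a canteen lunch, bought and eaten on campus, go?**

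| Rule | Source | Result |
|---|---|---|
| Home is for food not bought and eaten out | App section, instruction to participants | Not Home, but no matching code exists |
| Home takes anything not from the nine outlet types | Textbox 2, definition of Home | Home |
| Nearest-fit choice by the participant | Textbox 2, two independent categories | Away from home, merged with another outlet type |

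Under every row the cafeteria contribution cannot be separated out. Under the second row the item also moves from away-from-home to home.

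**Step 3: does anything later in the plan recover the item?**
- Data Cleaning provides for contact about freeform food entries and inconsistencies such as gross entry errors and skipped meals. Source location is not named.
- The Comparative Validation Substudy compares energy, nutrients and food groups, not food source.
- The Abstract mentions place of consumption as well as purchase, but the Methods describe no place-of-consumption field.
- The Demographic and Usability Questionnaire collects self-reported frequency of, and spending on, food bought and eaten out over the 3 days. This could reveal under-coding in total, but it does not identify the outlet.

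**Step 4: direction and size.** Let S be the true away-from-home share of intake and u the fraction of that intake coded Home. Then

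observed share = S × (1 - u), and bias = -S × u.

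The documents give neither S nor u. With assumed values, for illustration only:

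| Assumed S | u = 5% | u = 10% | u = 20% |
|---|---|---|---|
| 30% | 30 × 0.95 = 28.5% | 30 × 0.90 = 27.0% | 30 × 0.80 = 24.0% |
| 40% | 40 × 0.95 = 38.0% | 40 × 0.90 = 36.0% | 40 × 0.80 = 32.0% |

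Here u counts only what is actually coded Home. If 10% of away-from-home intake comes from unlisted outlets and half of it is entered under another outlet type, then u = 10% × 0.5 = 5%. A larger sample does not reduce the bias.

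**The case against.** The strongest reply is that participants were told to use Home only for food not bought and eaten out. Someone who follows that instruction would not choose Home for a canteen meal and would pick the nearest outlet. Independent café or restaurant is broad: it covers any cuisine, and its examples end with restaurants in general. Such entries still count as away from home, so the total share is not understated for them. The outlet list in the aims is also only illustrative, and the version of the objective in the Abstract does not mention cafeterias.

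Much of this stands. A reader might infer that every cafeteria or vending purchase is counted as home food; the instruction in the app section prevents that conclusion. The same reply limits any complaint about sit-down chain restaurants, which may be entered under a neighbouring category. It does not restore a cafeteria estimate, because merged entries cannot be separated again. Nor does it remove the conflict between the instruction and the definition of Home. The illustrative wording softens the promise, but cafeteria is still one of five outlets named.

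Two further inferences are tempting and unsupported. One is that the error falls mainly on students and employees and so biases regressions on study, employment or area; nothing in the documents shows who uses canteens or how they code them. The other is that the bias can be set against the stated margin of ±3%. Population Sampling gives that margin for estimates of proportions with 1008 participants. The precision of a mean energy share depends on its between-person spread, which is not given.

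**Conclusion.** The point holds as an inconsistency between the Aims, the instruction in the app section and the definition of Home in Textbox 2. The cafeteria contribution cannot be estimated with the list as printed, whichever way participants code such purchases. To the extent that they follow the Textbox 2 definition, the away-from-home share is biased downwards and the home share upwards by the same amount. That direction is certain for any purchase coded Home. The size is unknown: the shares in the working rest on assumed values of S and u, and u is zero if all participants choose another outlet type. The matter should be corrected, since it concerns the classification on which the main results rest, but the documents do not show that the overall away-from-home estimate is seriously wrong.

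**What to change.** **For new records.** Add two codes to the list: cafeteria/canteen, and other away from home with a text field. Restrict Home to the three things its description already names (homemade food, food from friends or relatives, supermarket food), so that Textbox 2 and the participant instruction agree. Query ready-to-eat items entered as Home at the check made in the 2 days after entry.

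**For records collected before the change.** Recruitment is already underway, and that 2-day check cannot reach entries whose window has passed. Flag the list version on each record. Report a sensitivity analysis that reclassifies ready-to-eat Home items as away from home, cross-checked against the self-reported away-from-home frequency in the final questionnaire. State that the cafeteria share is not estimable from these records.

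**If the app cannot be changed.** Reconcile the three places in the text, say how unlisted outlets were coded, drop cafeteria from the outlets to be reported separately, and declare the possible understatement.

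**Cost.** Two list items, a revised Home description, a version flag and one sensitivity analysis; no extra visits or participants. The drawback is that outlet coding then differs by list version, and so by enrolment date. Outlet-level results must therefore carry the version flag.

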### Study Design

A cross-sectional study of young adults aged 18 to 30 years who reside in New South Wales (NSW), Australia’s most populous state [26], will be conducted. Age 30 was chosen as a cut-off, because in Australia the median age of first-time mothers is 28.9 years, and the average age of all women giving birth is 30.3 [27]. The median age of first-time fathers is 33.1 [28]. The age bracket of 18 to 30 years was chosen to capture *young adulthood* —for many, before having their first child.

### Population Sampling

Purposive sampling will be conducted to ensure quotas for different demographics are captured. Individuals are eligible to enroll in the study if they: (1) are aged 18 to 30 years; (2) reside in NSW; (3) own or have access to a smartphone; (4) can read, write, and understand English; and (5) consume at least one meal, snack, or drink purchased outside the home per week. As the data will be collected using a smartphone app in English, it is important that the participants have access to a smartphone and are proficient in written English. The study is specifically focused on foods eaten away from home, so it is important that participants eat out at least once per week. Participants will be excluded if they do not meet the aforementioned criteria, are not able to commit to 3 consecutive days of data collection, are pregnant and/or breastfeeding, or have ever been diagnosed or treated for an eating disorder. Pregnant women and breastfeeding mothers will be excluded as their nutritional requirements, and potentially eating habits, change during this time. Those who have been diagnosed or treated for an eating disorder will be excluded because of ethical reasons.

A total of 1008 participants will be recruited to the study, across a range of geographic areas and demographic factors, which provides a margin of error of ±3% on all estimates of proportions (with 95% CI). An even spread of males and females will be recruited. The sample will be constituted to ensure an even distribution of participants in the older age bracket (25 to 30 years) and the younger age bracket (18 to 24 years); from metropolitan and regional areas (as defined by the Accessibility/Remoteness Index of Australia (ARIA+) [29] based on the postcode of the area the participant resides, with major cities considered “metropolitan” and all other areas “regional”); and from lower and higher SES areas (as defined by the Index of Relative Socio-economic Advantage and Disadvantage (IRSAD) [30] based on the postcode of the area where the participant resides) with “low” SES, including deciles 1-5 and “high” SES deciles 6-10). The sampling diagram is shown in Multimedia Appendix 1.

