### Screening and Consent

The screening survey (Textbox 1) will be administered at recruitment to collect basic demographic data and consent using the Web-based REDCap research management system [33]. The REDCap system will be programmed to screen participant demographics to fill the study’s demographic quotas. The REDCap system also allows stratified randomization in the substudy (refer to section below).

After completion of the screening questionnaire and enrollment, participants will be notified of their dietary data collection dates, and emailed instructions on how to download and sign up to use the Eat and Track (EaT) app, and obtain a user guide for the EaT app and a copy of the Australian Bureau of Statistics Food Model booklet [34] to assist with estimating portion sizes. Links to useful information on the study website will also be available, including an electronic version of the Food Model booklet.

The study website (Figure 2) was developed to provide information for those participating in this study and future participants. It contains information about the study, its funding and partners, links to the screening questionnaire, technical guides and videos for participants, and links to the Food Model booklet. Potential participants can also contact the study team via email through the website.

Participants will be taught how to use the app using instructional videos and will have access to these videos at all times throughout the study via the study website. Additionally, participants will need to view 3 tutorial screens in the app before they can start recording their intake. They will then record all food and drinks for 3 consecutive days.

Screening questionnaire.Demographics:AgeGenderAboriginality and ethnicityLanguage spoken at homeEducation attainmentPostal code of home addressLiving arrangementRelationship statusEmployment and studyIncomeScreening questions:Do you own a working smartphone?On average, do you have at least one drink, snack or meal you buy away from home each week?(Females only) To your knowledge, are you pregnant and/or breastfeeding?Have you ever been diagnosed or treated for (choose all that apply)?Anorexia Nervosa (screen out)Bulimia Nervosa (screen out)Other eating disorder (screen out)Mental illnessIllicit drug useDiabetesNone of these

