### Conclusions

This study is the first in Australia to provide detailed information on foods purchased and eaten out of home. By incorporating information from the largest fast food chains in Australia in the app’s food composition database, it is also the first dietary assessment app internationally to have a specific focus on eating out. The requirement of participants to record where they sourced each food or drink will also provide the first estimation of how often young Australians are eating out, and what proportion of their nutritional intake is derived from such meal occasions. This will enable the identification of foods and consumption behaviors of concern that should become the focus of future health promotion efforts for this target audience. Accurate and detailed measurement is important to ensure evidence-based programs.

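### Enrolment is limited to people who buy food or drink out at least weekly, but eating-out frequency and dietary share are presented as those of young adults in general

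*Protocol article*

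**What the plan says.** Population Sampling in the protocol article makes it an entry condition that people "consume at least one meal, snack, or drink purchased outside the home per week"; the abstract repeats this. The reason given is: "The study is specifically focused on foods eaten away from home, so it is important that participants eat out at least once per week". The screening questionnaire applies the rule with one self-report item: "On average, do you have at least one drink, snack or meal you buy away from home each week".

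The aims use a wider population: "The study will determine how frequently young adults purchase and consume foods away from home in the context of their entire diet", and "the extent to which food and beverages consumed away from home contribute to the total energy and nutrient intake of young adults". Knowledge Gaps describes the planned data as coming from a population sample of Australians in this age range. The closing Conclusions section claims the "first estimation of how often young Australians are eating out", and "what proportion of their nutritional intake is derived from such meal occasions".

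The analysis section on foods purchased and eaten away from home plans an average frequency and a relative contribution to energy and macronutrients in the enrolled sample. No section confines these estimates to weekly buyers, lists the entry rule as a limitation, or plans to count those it screens out.

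**The concern.** The entry rule is defined on the quantity being estimated. A mean taken only among people at or above a floor is a mean for those people. It is not the mean for the group that also contains everyone below the floor. The article explains why the rule exists, but the explanation does not carry over to the aims and conclusions, which speak of young adults and young Australians.

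At stake is the meaning of the headline figures. A reader of the eventual results would take average frequency and share of intake as describing all young adults, when they describe those already buying out at least weekly. The stated margin of ±3% gives no protection, because it covers sampling error only and a larger sample leaves this gap unchanged.

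**Working it through.** **1. The plan's own precision figure.** Inputs from Population Sampling: n = 1008, 95% confidence. With p = 0.5, the margin is 1.96 × √(0.25/1008) = 3.09%, which rounds to the stated ±3%. The figure is reproduced. It describes sampling error among the kind of people enrolled.

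**2. Effect of the entry rule alone.** Let q be the share of young adults below one purchase a week, m the mean among those eligible, and e the mean among those excluded.

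- Population mean = (1−q)·m + q·e
- Relative excess of the enrolled mean = m / [(1−q)·m + q·e] − 1

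For frequency, e is below one a week and m is at least one, so the excess is positive for any q > 0, provided people answer the screening item accurately. Since e cannot be negative, the excess is largest at e = 0, where it equals 1/(1−q) − 1.

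**3. Size.** The documents give neither q, m nor e, so all three are assumed here. The last column uses m = 5 and e = 0.5 purchases a week.

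| Assumed q | Ceiling (e = 0) | Excess with m = 5, e = 0.5 |
|---|---|---|
| 2% | 2.0% | 1.8% |
| 5% | 5.3% | 4.7% |
| 10% | 11.1% | 9.9% |
| 20% | 25.0% | 22.0% |

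Example at q = 10%: ceiling 1/0.90 − 1 = 11.1%; with e = 0.5, 5/(0.9×5 + 0.1×0.5) − 1 = 5/4.55 − 1 = 9.9%.

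**4. Dietary share.** The same identity applies to the mean of individual shares. The direction needs one further assumption: that less-than-weekly buyers get a smaller part of their intake from outside. Take an assumed 30% energy share among those enrolled and 0% to 5% among those excluded. The excess in percentage points is q × (30 − e):

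- q = 2%: 0.5 to 0.6
- q = 5%: 1.25 to 1.5
- q = 10%: 2.5 to 3.0
- q = 20%: 5 to 6

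On these assumptions it equals the stated 3-point margin when q is 3/30 = 10% (e = 0) to 3/25 = 12% (e = 5%).

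**The case against.** The rule is disclosed in the abstract, justified in the Methods, and sets a very low bar: a single bought coffee a week is enough. The excluded share could be so small that the effect is lost in the sampling error. At q = 2% it is at most 0.6 points on a 30% share, well inside ±3. This stands, and it is why no single figure can be attached to the effect.

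A reader might infer that the results are shown to be too high. The documents do not support that. Recruitment is purposive and voluntary, through a charity, a university and snowball contacts, and may shift the estimates either way. What follows is the direction of this one criterion, not of the net bias. Nor are the percentages above estimates: each is a maximum at its assumed q.

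A reader might also infer that losing infrequent buyers weakens the associations sought in the regressions and data mining. That is not established. People at one or two items a week remain eligible, and recording covers only 3 days. If purchases follow a Poisson process (an assumption), someone at one a week records none with probability exp(−3/7), about 65%. Low and zero observed values therefore stay in the data.

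The planned comparison with the national survey concerns total energy and nutrient intakes. Knowledge Gaps says the latest national nutrition survey did not record food source, so no eating-out figure is benchmarked there. The mix of outlets within away-from-home intake and the app validation are little affected.

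None of this reconciles the entry rule with the population named in the aims and conclusions.

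**Conclusion.** The point holds as a mismatch between the population enrolled and the population claimed. Considered alone, the weekly-purchase rule raises mean frequency for young adults in general by at most 1/(1−q) − 1: about 2%, 5%, 11% and 25% at assumed q of 2%, 5%, 10% and 20%. The same ceiling applies to dietary share, and there the upward direction is very probable but not certain. The result rests on accurate answers to the screening item and, for share, on less-than-weekly buyers having the smaller share. With q unknown, the true effect may be negligible or may exceed the stated margin of error. Net overstatement is not demonstrated. The choice of entry rule is defensible for a study of eating out; the unqualified claims are what need to change.

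**What to change.** - In the aims, the conclusions and the comparison with national survey intakes, state the target population as 18- to 30-year-olds in New South Wales who buy food or drink away from home at least weekly.
- Report the number and share of people answering no to the existing screening item, by quota cell.
- If a figure for all young adults is wanted, show it only as a sensitivity range over assumed q, with the assumed intake of excluded people stated. The screening pool is not a probability sample, so its share of negative answers should not be used as an estimate of q in the population.

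The cost is a change of wording and one table from an item already asked at screening. Eligibility, sample size and data collection stay as they are. The downside is a narrower headline claim.
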